## **List of abbreviations**

|         |                                                                    |
|---------|--------------------------------------------------------------------|
| ED:     | Emergency department                                               |
| eCRF:   | electronic case report form                                        |
| FiO2:   | Fraction of inspired oxygen                                        |
| GCP:    | Good Clinical Practice                                             |
| ICU:    | Intensive care unit                                                |
| ITT:    | Intention-to-treat                                                 |
| IV:     | Intravenous                                                        |
| LOS:    | Length of stay                                                     |
| MAP:    | Mean arterial pressure                                             |
| PaO2:   | Partial pressure of oxygen                                         |
| RRT:    | Renal replacement therapy                                          |
| SAE:    | Serious adverse event                                              |
| SAR:    | Serious adverse reaction                                           |
| SOFA:   | Sequential organ failure assessment                                |
| SPIRIT: | Standard Protocol Items: Recommendations for Interventional Trials |
| SSC:    | Surviving Sepsis Campaign                                          |
| SUSAR:  | Suspected unexpected serious adverse reaction                      |

## Overview

|                                         |                                                                                                                                                                                                                                                                                                                                                                                                                                                                                                                                                                      |
|-----------------------------------------|----------------------------------------------------------------------------------------------------------------------------------------------------------------------------------------------------------------------------------------------------------------------------------------------------------------------------------------------------------------------------------------------------------------------------------------------------------------------------------------------------------------------------------------------------------------------|
| Registry and trial number               | EudraCT number: 2021-000224-35, ClinicalTrials.gov number: NCT05076435                                                                                                                                                                                                                                                                                                                                                                                                                                                                                               |
| Date of registration                    | EudraCT: 2021-05-03, ClinicalTrials.gov: 2021-10-13                                                                                                                                                                                                                                                                                                                                                                                                                                                                                                                  |
| Sources of monetary or material support | Carl and Ellen Hertz foundation, Frimodt-Heineke Foundation, Ruth & Holger Hesses Memorial Fund, Health Research Foundation of Central Denmark Region, "Akutpuljen" Central Denmark Region, and Aarhus University                                                                                                                                                                                                                                                                                                                                                    |
| Sponsor-investigator                    | [name] on behalf of Aarhus University                                                                                                                                                                                                                                                                                                                                                                                                                                                                                                                       |
| Contact                                 | [name], [contact]                                                                                                                                                                                                                                                                                                                                                                                                                                                                                                                                  |
| Title                                   | Restrictive Fluid Administration vs. Standard of Care in Emergency Department Sepsis Patients - a Multicenter, Randomized Clinical Feasibility Trial (REFACED Sepsis)                                                                                                                                                                                                                                                                                                                                                                                                |
| Country of recruitment                  | Denmark                                                                                                                                                                                                                                                                                                                                                                                                                                                                                                                                                              |
| Condition studied                       | Sepsis                                                                                                                                                                                                                                                                                                                                                                                                                                                                                                                                                               |
| Interventions                           | Restrictive intravenous fluid administration                                                                                                                                                                                                                                                                                                                                                                                                                                                                                                                         |
| Comparator                              | Standard intravenous fluid administration                                                                                                                                                                                                                                                                                                                                                                                                                                                                                                                            |
| Inclusion criteria                      | 
All of the below criteria fulfilled:
 

1) Unplanned emergency department admission

2) Age <math>\geq</math> 18 years

3) Sepsis defined as

a) suspected infection by the treating clinician AND

b) blood cultures drawn AND

c) IV antibiotics administered or planned AND

d) infection-related increase of SOFA-score <math>\geq</math> 2

4) Expected hospital stay > 24 hours as deemed by treating clinician

 |
| Exclusion criteria                      | 
Any of the following:
 

1) <math>\geq</math> 500 ml of fluids given prior to randomization

2) Invasively ventilated or vasopressors

3) Known or suspected severe bleeding

4) Known or suspected pregnancy

5) Prior enrollment in the trial

6) Patients, who the clinician expect not to survive the next 24-hours

                                                                                                                                                       |

|                         |                                                                                                                                                                                                                                                                                                                                                                                                                                                                 |                              |
|-------------------------|-----------------------------------------------------------------------------------------------------------------------------------------------------------------------------------------------------------------------------------------------------------------------------------------------------------------------------------------------------------------------------------------------------------------------------------------------------------------|------------------------------|
| Study type              | Interventional                                                                                                                                                                                                                                                                                                                                                                                                                                                  | Allocation: Randomized (1:1) |
|                         | Intervention model: Parallel group                                                                                                                                                                                                                                                                                                                                                                                                                              | Masking: None                |
| Date of first screening | To come                                                                                                                                                                                                                                                                                                                                                                                                                                                         |                              |
| Target sample size      | 124                                                                                                                                                                                                                                                                                                                                                                                                                                                             |                              |
| Recruitment status      | Planning                                                                                                                                                                                                                                                                                                                                                                                                                                                        |                              |
| Primary outcomes        | 24-hour intravenous crystalloid fluid administration                                                                                                                                                                                                                                                                                                                                                                                                            |                              |
| Key secondary outcomes  | Feasibility measures: 
 
• Number of patients with major protocol violations,
 
• Number of patients screened vs included
 
• Time from admission to inclusion
 
• Number of patients lost to follow up in terms of 24-hour fluids
 
• Accumulated serious adverse reactions and events (SARs + SUSARs) within 48 hours in-hospital
 
 Total fluids (oral and intravenous) at 24 hours, |                              |

## Trial flow chart

[figure not shown]

## Conflicts of interest

The members of the steering committee have no conflicts of interest related to the current trial. A list of all conflict of interests is provided in Appendix 1.

## Amendments

### Version 1.0 to 1.1

- Clarification of data collection of pre-enrollment data (section 7.1.2)
- Clarification of screening and enrollment process (section 8.1)
- Clarification of consent and access to data from authorities (section 9.3.2)
- Clarification of publication of results regardless of outcome (section 12)

### Version 1.1 to 1.2

- Safety and harm: Addition of section describing timing and classification of adverse events (section 5.4.3) and reporting (section 5.4.6) + appendix 3 (new version)
- Clarification that the precise IMP has to be noted on paper-CRF (section 7.1)
- Clarification of uploading process to EudraCT as soon as possible (section 12)

### Version 1.2 to 1.3

- Clarification of end-of-trial report and notice to EudraCT (section 5.4.6)

### Version 1.3 to 2.0

- Clarification of the acute medical trial and inclusion (section 9.2.3 and 9.3.2)
- Clarification of collection of data on screened patients (section 7.1.2)
- Clarification of consent procedures (section 9.3.2)

### Version 2.0 to 2.1

- Clarification of collection of data on screened patients (section 7.1.2)

### Version 2.1 to 2.2

- Addition of registration data from EudraCT and Clinicaltrials.gov
- Clarification of statistics (section 6.2.2)
- Clarification of screening population and successful inclusion (section 5.2.1 and 7.1.2)
- Clarification of collected data-variables i.e. comorbidities, timing of SOFA-score etc. (section 7.1.2+7.1.6 +7.1.9)

#### Version 2.2 to 2.3

- Correction of statistics in secondary outcomes (section 6.2)

## **1. BACKGROUND**

### **1.1 Sepsis – the participant population**

#### *1.1.1 Incidence and mortality*

Sepsis is very common in emergency department (ED) patients. Sepsis and suspected infection accounts for approximately 43% of all patient admissions in a Danish medical ED and sepsis accounts for more than 500,000 yearly patient visits in the United States. Patients presenting to the ED with suspected infection and sepsis are at risk of disease progression to septic shock (7-26%) and ultimately death with mortality ranging from 10 to 23%. It has been estimated that 15% of all deaths in Denmark are caused by sepsis. In addition, the morbidity and effect on health-related quality of life after sepsis is significant.

#### *1.1.2 Pathophysiology and definition*

Sepsis is defined as life-threatening organ-dysfunction caused by a dysregulated host-response to infection. Sepsis is not a specific illness but rather a syndrome encompassing a still-uncertain pathobiology. It can be identified by a constellation of clinical signs and symptoms in a patient with suspected infection caused by an entering bacteria, virus or fungi activating the immune system. Sepsis is a heterogeneous disease with a variety of sources of infection causing variable degrees of organ dysfunctions. The most frequent sources of infection are pneumonia, abdominal, urinary tract, and soft tissue infections.

Sepsis is defined in accordance with the SOFA-score. SOFA-score reflects organ dysfunction in the following organs/systems: respiratory, coagulation, liver, cardiovascular, central nervous system, and renal (see appendix 2). Sepsis is present if the patient has a suspected or verified infection and an increase in SOFA-score  $\geq 2$  from baseline caused by or suspected to be caused by the infection.

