### **4.2 Inclusion criteria**

The research team, clinically working nurses and ED physicians will screen ED patients for the following inclusion criteria:

- 1) Unplanned emergency department admission
- 2) Age  $\geq 18$  years
- 3) Sepsis defined as
  - a) suspected infection by the treating clinician AND
  - b) blood cultures drawn AND
  - c) IV antibiotics administered or planned AND
  - d) An infection related increase of SOFA-score  $\geq 2$  from baseline
- 4) Expected hospital stay > 24 hours as deemed by treating clinician

These broad inclusion criteria were chosen to investigate the effect of fluid administration in the entire, broad sepsis population and increase the likelihood of describing the entire 24 hours inclusion period. We will strive to enroll participants as soon as they fulfill the criteria in the ED. There is no exact maximum time frame for patient inclusion, however with the exclusion criteria of > 500 ml. IV fluids administered, the inclusion is expected and intended to happen within the first couple of hours.

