#### *7.1.6 Variables obtained at 6-, 12- and 24 hours after randomization:*

Hourly volumes of resuscitation fluid with specification of indication for each fluid bolus

Other fluids including blood products, nutrition, fluid with medication

Highest creatinine within 24 hours to evaluate KDIGO-criteria

Only 24hours: To evaluate worst SOFA-score within 24 hours:

Results of blood samples (standard lab. Values + arterial/venous blood gas)

- Lowest values: platelets, PaO2 (and FiO2)
- Highest values: lactate, bilirubin,

Use of renal replacement therapy Y/N

Protocol violations

Non-invasive ventilation Y/N

On mechanical invasive ventilation or vasopressor Y/N

Status: dead, Y/N

Only 24hours: SAEs (see section 5.4.3) + SARs (see section 5.4.4)

SAEs on this day (y/n for everyone)

- Cerebral ischemic event
- Myocardial ischemic event
- Intestinal ischemic event
- Limb ischemia
- New onset of severe acute kidney injury

SARs on this day (y/n for everyone)

- General tonic-clonic seizures
- Anaphylactic reactions
- Central pontine myelinolysis
- Severe hyponatremia
- Severe hyperchloremic acidosis
- Severe metabolic alkalosis

Only 24 hours: SUSARs

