## Appendix 2: Sequential organ failure assessment (SOFA) score

The Sequential organ failure assessment (SOFA)-score is in the current study defined in accordance with The Third International Consensus Definitions for Sepsis and Septic Shock (Sepsis-3)

| Sequential [Sepsis-related] Organ-Failure Assessment Score adapted from Sepsis-3                                                                                                                                                                                                                                                                                                                                                                                                                                                                                                                                                  |               |               |                                                    |                                                                           |                                                                         |
|------------------------------------------------------------------------------------------------------------------------------------------------------------------------------------------------------------------------------------------------------------------------------------------------------------------------------------------------------------------------------------------------------------------------------------------------------------------------------------------------------------------------------------------------------------------------------------------------------------------------------------------------|---------------|---------------|----------------------------------------------------|---------------------------------------------------------------------------|-------------------------------------------------------------------------|

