| Urine output, mL/d                                                                                                                                                                                                                                                                                                                                                                                                                                                                                                                                                                                                                             |               |               |                                                    | < 500                                                                     | < 200                                                                   |
| 
The table shows the scoring of organ dysfunctions with the Sequential [Sepsis-related] Organ-Failure Assessment Score. The final SOFA-score is calculated summing all sub-scores from each organ system. Only definitions with units used in Danish emergency departments are shown.
 
Abbreviations: PaO2: Partial pressure of oxygen, FiO2: Fraction of inspired oxygen, MAP: Mean arterial pressure
 
a Catecholamine doses are given as μg/kg/min for at least 1 hour
 
b Glasgow Coma Scale Scores range from 3-15: Higher scores indicate better neurological function
 |               |               |                                                    |                                                                           |                                                                         |

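### The SOFA table in Appendix 2 prints no renal score for creatinine 401–440 µmol/L, a 1-point ambiguity that can decide entry only for some patients with pre-existing renal dysfunction

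*Protocol*

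**What the plan says.** Section 1.1.2 introduces the score and its six organ systems: "SOFA-score reflects organ dysfunction in the following organs/systems: respiratory, coagulation, liver, cardiovascular, central nervous system, and renal (see appendix 2"). It defines sepsis as suspected or verified infection with a rise of at least 2 points from baseline. Section 4.2 makes this inclusion criterion 3d, "An infection related increase of SOFA-score" of 2 or more, and cites the Sepsis-3 reference there.

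Appendix 2 says that the score "is in the current study defined in accordance with The Third International Consensus Definitions for Sepsis and Septic Shock" (Sepsis-3). Its renal row gives these creatinine bands in µmol/L:

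| Points | 0 | 1 | 2 | 3 | 4 |
|---|---|---|---|---|---|
| Creatinine | < 110 | 110–170 | 171–299 | 300–400 | > 440 |

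A second renal line, "Urine output, mL/d", gives 3 points below 500 and 4 points below 200. On the total, the appendix states: "The final SOFA-score is calculated summing all sub-scores from each organ system".

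The score is used in three further places. Section 7.1.5 collects the values for SOFA at admission. Section 7.1.6 collects data at 24 hours under "Only 24hours: To evaluate worst SOFA-score within 24 hours". The screening log in section 8.1.2 records whether SOFA is at least 2, from laboratory values.

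**The concern.** A scoring table that supports an inclusion criterion should give every laboratory value exactly one score. This one does not: the 3-point band stops at 400 and the 4-point band begins above 440. Two people scoring the same patient with a creatinine of 420 can reach totals that differ by 1 point, and both can say that they followed the appendix.

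The entry rule is a threshold on a change from baseline, so 1 point can matter at the margin. The gap can also fall on the baseline value, because section 7.1.3 collects habitual creatinine. Kidney disease is not an exclusion in section 4.3, so patients with raised habitual values can enter. At stake are consistent eligibility decisions for a small group and a 1-point inconsistency in a descriptive severity score.

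**Working it through.** **1. Find the gap.** I coded the creatinine row as printed and tested every whole value from 30 to 1200 µmol/L. The unscored values are exactly 401 to 440, which is 40 values. The other joins in the row meet (170/171 and 299/300). The same test on the bilirubin row finds no unscored whole value. The platelet row uses nested cut-offs and the Glasgow Coma Scale row is contiguous. The creatinine gap is therefore not the table's usual layout.

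**2. Bound the score.** The bands rise with creatinine. A value of 401–440 exceeds everything in the 3-point band and is below everything in the 4-point band, so on any ordered reading it scores 3 or 4. Urine output below 200 mL/d would give 4 and settle the matter. Below 500 mL/d gives only 3 and does not. Sections 7.1.5 and 7.1.6 do not name urine output, and a daily volume is not known at screening, which section 4.2 intends within the first couple of hours.

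**3. Entry rule, admission creatinine in the gap.** Let p be the renal score at admission (3 or 4), b the baseline renal score, and o the rise from the other organs, with o at least 0. The patient qualifies if p − b + o ≥ 2. The choice of p matters only when 3 − b + o = 1, that is, when o = b − 2.

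| Baseline renal score b | Rise with o = 0 (p = 3 / p = 4) | o at which the choice decides | Total rise there (p = 3 / p = 4) |
|---|---|---|---|
| 0 | 3 / 4 | none | – |
| 1 | 2 / 3 | none | – |
| 2 | 1 / 2 | 0 | 1 / 2 |
| 3 | 0 / 1 | 1 | 1 / 2 |
| 4 | −1 / 0 | 2 | 1 / 2 |

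So with b = 0 or 1 the patient qualifies on the renal item alone, whichever score is used.

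**4. Entry rule, baseline creatinine in the gap.** Now b is 3 or 4. If admission creatinine is above 440 (4 points), the rise is 1 + o or 0 + o, and the choice decides only at o = 1 (2 against 1). If admission creatinine is 300–400 (3 points), the rise is 0 + o or −1 + o, and the choice decides only at o = 2 (2 against 1). If both values are in the gap and are scored alike, the renal rise is 0 either way. All these patients have a baseline renal score above 2.

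**5. Worst SOFA within 24 hours.** The ambiguity is 4 − 3 = 1 point.

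**6. How many patients.** The Protocol gives no creatinine distribution, so this step is assumption only. For a lognormal with median m and log-SD s, the share in the gap is Φ(ln(440.5/m)/s) − Φ(ln(400.5/m)/s).

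| m (µmol/L) | s | Share in gap | × 124 randomized |
|---|---|---|---|
| 100 | 0.5 | 0.1% | 0.2 |
| 110 | 0.6 | 0.5% | 0.7 |
| 130 | 0.7 | 1.3% | 1.7 |
| 150 | 0.8 | 2.1% | 2.6 |

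These figures count every admission value in the gap. Eligibility turns only in the subset identified in steps 3 and 4, which the documents do not allow me to size. Counts among randomized patients also say nothing about patients turned away.

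**The case against.** The strongest reply is that Appendix 2 is not the only authority. Criterion 3d cites Sepsis-3 directly and the appendix says it follows that definition, so an assessor in doubt can go to the source. The raw creatinine is collected at randomization and as the highest value within 24 hours, so scores can be recomputed later. Detailed variable definitions are left to a data dictionary. The table was also read from PDF by a program, and a single misread digit could produce the gap. All of this stands and limits the consequence. It does not remove the defect in the text at hand: the appendix is the table that section 1.1.2 refers to, it is meant for use at the bedside, and recomputing a score later does not reverse an enrolment decision.

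A reader might infer more: that a patient with creatinine 401–440 cannot be scored at all, that 3 or 4 points are lost, or that clearly eligible patients are turned away. The documents do not support this. Each of these needs someone, or some formula, to give nothing to a value higher than one that scores 3. The Protocol describes no automated SOFA calculation, so such a formula is a possibility to guard against and not a finding. Step 3 shows that a patient with little or no prior renal dysfunction qualifies on either reading.

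**Conclusion.** The table is wrong as written, and the consequence is minor. Creatinine 401–440 µmol/L has no printed score in Appendix 2, which leaves a 1-point ambiguity in the admission SOFA and in the worst SOFA within 24 hours. It can change eligibility only at baseline renal score 2 or more, and there only in the combinations in steps 3 and 4. Neither the primary outcome (section 5.1.1) nor any outcome listed in section 5.2.1 uses SOFA, so the main comparison is unaffected.

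This rests on three assumptions: that creatinine is reported in whole µmol/L, that the bands are read as ordered, and that other organs have not improved from baseline. The numbers of patients rest on assumed distributions and show only that few are involved.

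**What to change.** Check the creatinine row on the printed page, then against the Sepsis-3 source table that the appendix cites. Correct whichever limit differs, so that the bands are contiguous and every value has exactly one score. The source is not at hand here, so I do not say which limit is in error. Use the corrected row in the data dictionary, the screening-log SOFA check and the SOFA values held in REDCap, and test one value between 401 and 440 in each. If patients have already been screened, rescore those with a baseline or admission creatinine in that range from the recorded values. The cost is one table cell and a short check of the data definitions. The sample size and the planned analyses do not change.
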